#### Procedure

The procedure flow for patient recruitment is summarized in Fig. 3. Upon consultation from the emergency department physician, a member of the orthopaedic team (resident, staff physician or physician assistant) will meet patients presenting with an acute Achilles tendon rupture. The orthopaedic team will confirm the diagnosis, discuss the diagnosis and management options with the patient. Concurrently, they will verify if the patient meets inclusion criteria, discuss the study procedures, answer patients’ questions, and obtain the patients’ signed consent to participate. The patient will be asked to complete a baseline questionnaire including questions about their demographics (age, sex, gender, occupation, highest level of education) and secondary outcome measures. The patient will be splinted in plantarflexion in keeping with standard practice and given a copy of the PtDA to review and complete in preparation for their follow-up appointment in the orthopaedic clinic.

**Fig. 3 Fig3:**
[figure not shown]
Patient participant study procedure

As per usual clinical practice, patients will be given a follow-up appointment in the orthopaedic plaster room 3–5 days following their emergency department visit. At the plaster room, the orthopaedic resident or surgeon will discuss the treatment options, answer patients’ questions and make the treatment decision with the patient. Either immediately following or within 2 weeks, the research assistant will ask the patient to complete a questionnaire including the secondary outcome measures and conduct the semi-structured interview.

We will also obtain feedback from orthopaedic residents and surgeons who consulted with patients in the study to determine the clinician experience with patients using the PtDA. After the last patient is recruited, these orthopaedic surgeons will be sent a link to an online survey using the SurveyMonkey (San Mateo CA) platform to elicit feedback on the PtDA.

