#### Outcomes and instruments

Field test outcomes of interest have been chosen based on those recommended by IPDAS [18]. Field test outcomes are summarized in Table 1 and include: (1) feasibility of PtDA administration and use by patients, (2) barriers to PtDA use among patients and clinicians, (3) patients’ acceptability of the PtDA, and (4) potential of the PtDA to have the desired impact without adverse consequence.

**Table 1 Tab1:** Summary of field test outcome measures

Outcome	Instruments	Measure of Success
1. Feasibility		
a. Patients		
	Metrics of use	At least 80% recruitment
		At least 80% PtDA completion
		At least 80% data completion
b. Surgeons	Patient semi-structured interview	Identifying resolvable barriers to PtDA use
	Metrics of use	At least 80% use for eligible patients
	Surgeon survey	Identifying resolvable barriers to PtDA use
2. Acceptability		
Amount of information	Post-PtDA	At least 66% perceive as acceptable
Length	Patient acceptability questionnaire	
Clarity		
Balance of presentation		
3. Potential for PtDA to have desired effect without adverse consequence		
	Post-PtDA	
	Patient preparation for decision making scale (PDMS)	Score of at least 66/100
	Practitioner preparation for decision making scale (PDMS)	Score of at least 66/100
	Pre- and post-PtDA	
	Knowledge test	At least 66% demonstrate improvement from pre to post PtDA administration
	SURE test	66% demonstrate improvement from pre to post PtDA administration
		And/or:
		> 66% Score 4/4 on post PtDA SURE test

Specific patient feasibility metrics will include the (1) percent of screened eligible patients recruited, (2) reasons for ineligibility, (3) percentage of recruited patients that completed the PtDA prior to the follow-up appointment and the (4) percentage of missing data on follow up outcome questionnaires. We will set a level of success at 80% participant recruitment of those meeting eligibility, 80% participant completion of the PtDA, and 80% minimal completed data on follow up questionnaires, in keeping with levels set in previously performed field tests [48].

The semi-structured interview with the patients will ask them to share their experiences on using the PtDA, their experiences discussing the decision with the orthopaedic surgeon, suggestions to improve the process of using the PtDA, formatting, and any barriers to use.

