The survey of orthopaedic surgeons will ask questions about how the PtDA influenced the patient-surgeon encounter. Data collected will aim to quantify experience with the PtDA including (1) number of times and reasons the PtDA was used or not used for eligible patients, (2) if they plan to continue to use the PtDA and (3) barriers and facilitators to implementation in usual clinical care. Specific feedback will be sought with respect on how and when the PtDA can best be administered in the patient journey to optimize uptake by both clinicians and patients. As part of the survey, we will also use the 11-question practitioner version of the PDMS to evaluate clinician views on how effective the PtDA was on the patient encounter [51].

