#### Data management and analysis

Quantitative data will be uploaded and stored in an encrypted Microsoft Excel spreadsheet. As the focus of the field test is on feasibility rather than efficacy outcomes, analysis will be primarily descriptive with baseline participant characteristics and feasibility data presented using frequencies and percentages. Tests for data normality will be performed and summarized using means and standard deviation if normally distributed, and medians and ranges if not. For post-test only outcomes (acceptability, PDMS), patients’ responses will be summarized and described. For pre-/post-test outcomes (knowledge and SURE test), questionnaires will be compared using the student t-test if normally distributed and using the Wilcoxon rank-sum test if not. Data will be disaggregated by sex and gender to examine how these variables may affect patient and clinician experience with the PtDA and associated outcome measures. Qualitative data from the semi-structured interviews will be transcribed verbatim and analyzed using thematic analysis as described for alpha testing.

There are no known defined standards for determining success of field testing measures. As such, we have determined the following a-priori criteria as determinants for success of the field test: (1) no insurmountable barriers identified from semi-structured interviews or open-ended feedback based on review from the steering group, (2) minimum of 80% targets for feasibility outcomes, (3) minimum of 66% of participants find the PtDA acceptable and balanced, (4) minimum score of 66 on the PDMS (5) 66% demonstrate nominal improvement on pre-/post-test outcomes for desired impact (knowledge and SURE). For the SURE test, an overall finding of > 66% participants responding with a 4/4 score will also be deemed a measure of success. If the cutoffs for determining success of the field test are not reached, revisions to the PtDA will be discussed and implemented by the steering group with further recruitment and testing at the discretion of the steering group.

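### The clinician survey reaches only clinicians with an enrolled patient, although it must explain non-use and barriers across all eligible patients

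*Protocol article*

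**What the plan says.** Stage 3, Procedure, defines the clinician group: "We will also obtain feedback from orthopaedic residents and surgeons who consulted with patients in the study". The link goes out once, after the last patient is recruited: "these orthopaedic surgeons will be sent a link to an online survey". Study patients are those who signed consent in the emergency department and were handed the aid there.

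Stage 3, Outcomes and instruments, gives the survey three factual tasks. The first is to record the "number of times and reasons the PtDA was used or not used for eligible patients". The other two are intention to continue using the aid, and barriers and facilitators in usual care. The practitioner PDMS is part of the same survey.

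Table 1 lists two surgeon feasibility criteria. One is "At least 80% use for eligible patients", with use metrics named as its instrument. The other is "Identifying resolvable barriers to PtDA use", with the surgeon survey as its instrument. Data management and analysis makes the 80% feasibility targets success criteria and adds a barrier criterion: "no insurmountable barriers identified from semi-structured interviews or open-ended feedback".

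**The concern.** The people asked and the question put to them do not match. Enrolled patients receive the aid as a study procedure, so the plainest case of non-use is an eligible patient who was never enrolled. The clinician who can say why is the one who saw that patient. If none of that clinician's patients was enrolled, the survey never reaches them.

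Feasibility is the primary outcome of the field test, and clinician barriers are part of it. Reasons such as lack of time in the emergency department, not knowing about the study, or reluctance to offer the aid would be concentrated among clinicians without enrolled patients. If they are not asked, the steering group could find no insurmountable barrier because the clinicians who met one were outside the survey. A use percentage built from survey replies would lean the same way.

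**Working it through.** **Inputs from the article.** Case volume is 60 per year, or 5 per month (Stage 3, Participants). The target is 30 patients at 3 per month over 10–12 months (Sample size). The recruitment and use targets are 80% each (Table 1). The numbers of clinicians and of eligible patients are not given.

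**1. The plan's own figure.** 30 / 3 = 10 months. At the upper end, 30 / 12 = 2.5 per month. This agrees with the stated 10–12 months.

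**2. Patients outside the study.** Expected ruptures are 5 × 10 = 50 to 5 × 12 = 60. With 30 enrolled, 50 − 30 = 20 to 60 − 30 = 30 are not enrolled. Some will be ineligible; the article does not say how many.

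**3. Frame against target.**

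| Item | Population |
|---|---|
| Clinicians surveyed | Those who consulted with an enrolled patient |
| Survey item on use and non-use | Eligible patients |
| Table 1 use target | Eligible patients |
| Recruitment target | Screened eligible patients |

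Three kinds of clinician follow:
- saw a study patient and used the aid: surveyed;
- saw a study patient and did not use the aid: surveyed, and asked why;
- saw eligible patients, none enrolled: not surveyed.

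**4. How far a use figure could move (assumed inputs).** Suppose recruitment is exactly 80%. Then 30 / 0.80 = 37.5 patients are eligible and 7.5 are not enrolled. Suppose the aid is used for 27 of the 30 enrolled and for no one else.
- Over enrolled patients: 27 / 30 = 90%, which passes.
- Over all eligible: 27 / 37.5 = 72%, which fails.

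If k unenrolled eligible patients are counted, use is 27 / (30 + k). It equals 80% at k = 27 / 0.80 − 30 = 3.75. Four are enough to change the result: 27 / 34 = 79.4%. Surveyed clinicians may report some of their own unenrolled patients, so a survey-based figure in this example would lie between 72% and 90%.

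**5. Does the recruitment target catch this?** In step 4, if all 37.5 were screened, recruitment is 30 / 37.5 = 80%, which just passes. If the 7.5 were never screened, it is 30 / 30 = 100%. For a larger gap, assume eight clinicians with equal flow, two of whom enrol nobody. If everyone is screened, recruitment is at most 6 / 8 = 75% and misses 80%. If those two clinicians' patients are never screened, they do not enter the metric.

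**The case against.** The strongest case against is that the frame suits the stated purpose of learning how clinicians experienced patients who used the aid, and that other criteria cover non-use. Much of this stands.

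- A reader might infer that clinicians who did not adopt the aid cannot count against the criteria. The text does not support that. Selection is on having consulted with a study patient, not on having used the aid. A plaster-room clinician who ignores a completed aid is in the frame and is asked for reasons.
- A reader might infer that the practitioner PDMS target, "Score of at least 66/100", is inflated by the frame. It is not. The scale rates what the aid did for an encounter, so a clinician with no such encounter has nothing to rate.
- A reader might fault the absence of a minimum survey response, since "80% minimal completed data on follow up questionnaires" stands among the patient metrics. A journal article may leave a survey response target to the full protocol, which is not shown. Silence here is no finding.
- Table 1 lists use metrics separately from the survey, so the 80% use figure is not shown to come from survey replies. However, the only described count of clinician use is the survey item, so the source is at best unclear.
- Recruitment counts unenrolled patients, but only if they were screened, and the orthopaedic team that sees the patients is also the one that checks eligibility.
- Barriers are also sought in patient interviews and, earlier, in alpha testing. Field-test interviews cover enrolled patients only, and alpha testing precedes use in the clinic. Neither reaches the clinician with no enrolled patient.

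**Conclusion.** The point holds in a limited form. Clinicians who saw eligible patients but had none enrolled are left out of a survey meant to explain non-use and barriers among eligible patients. The barrier evidence therefore leans toward clinicians who engaged with the study, and so does any use figure taken from the survey.

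The size of the lean on barriers cannot be computed, because the article gives no number of clinicians. For use, the illustration moves 90% to 72%. It assumes recruitment at exactly 80%, use for 27 of 30 enrolled, no use outside the study, and no unenrolled patient counted by the surveyed clinicians. If almost all eligible patients are enrolled, or every clinician on the rota has a study patient, the effect largely disappears. This is a modest weakness in a descriptive field test whose authors already call its success endpoints arbitrary, but it touches the primary outcome and is easy to remove.

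**What to change.** - Send the use and barrier items to every orthopaedic clinician, residents included, who covered emergency consults or the plaster room during recruitment, whether or not they had a study patient.
- Keep the practitioner PDMS for clinicians who had an encounter with the aid.
- Report the numbers invited, responding, and without such an encounter.
- Count use from study records over all eligible patients, including those not enrolled, and use the survey only for reasons. Say how a patient who declines is counted, because willingness to consent is itself an eligibility criterion.

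The cost is a longer mailing list for an online link already planned, a record of eligible patients who were not enrolled, and a line in Table 1. The use figure may also be lower: if only enrolled patients get the aid, it equals recruitment times use among the enrolled (0.80 × 0.90 = 0.72 in the example). The team should keep that in mind when reading it against 80%.

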#### Outcomes and instruments

Field test outcomes of interest have been chosen based on those recommended by IPDAS [18]. Field test outcomes are summarized in Table 1 and include: (1) feasibility of PtDA administration and use by patients, (2) barriers to PtDA use among patients and clinicians, (3) patients’ acceptability of the PtDA, and (4) potential of the PtDA to have the desired impact without adverse consequence.

**Table 1 Tab1:** Summary of field test outcome measures

Outcome	Instruments	Measure of Success
1. Feasibility		
a. Patients		
	Metrics of use	At least 80% recruitment
		At least 80% PtDA completion
		At least 80% data completion
b. Surgeons	Patient semi-structured interview	Identifying resolvable barriers to PtDA use
	Metrics of use	At least 80% use for eligible patients
	Surgeon survey	Identifying resolvable barriers to PtDA use
2. Acceptability		
Amount of information	Post-PtDA	At least 66% perceive as acceptable
Length	Patient acceptability questionnaire	
Clarity		
Balance of presentation		
3. Potential for PtDA to have desired effect without adverse consequence		
	Post-PtDA	
	Patient preparation for decision making scale (PDMS)	Score of at least 66/100
	Practitioner preparation for decision making scale (PDMS)	Score of at least 66/100
	Pre- and post-PtDA	
	Knowledge test	At least 66% demonstrate improvement from pre to post PtDA administration
	SURE test	66% demonstrate improvement from pre to post PtDA administration
		And/or:
		> 66% Score 4/4 on post PtDA SURE test

Specific patient feasibility metrics will include the (1) percent of screened eligible patients recruited, (2) reasons for ineligibility, (3) percentage of recruited patients that completed the PtDA prior to the follow-up appointment and the (4) percentage of missing data on follow up outcome questionnaires. We will set a level of success at 80% participant recruitment of those meeting eligibility, 80% participant completion of the PtDA, and 80% minimal completed data on follow up questionnaires, in keeping with levels set in previously performed field tests [48].

The semi-structured interview with the patients will ask them to share their experiences on using the PtDA, their experiences discussing the decision with the orthopaedic surgeon, suggestions to improve the process of using the PtDA, formatting, and any barriers to use.

Acceptability of the PtDA, will be evaluated using the OAT[49] previously used in the alpha test phase. This validated instrument measures key outcomes including; amount of information, length, clarity and balanced presentation, which is important for avoiding biased presentation of information on options.

To evaluate whether the PtDA potential to have the desired impact without adverse consequence, patients will complete a knowledge test[50] and the SURE test[31] as a pre-/post-outcome and the Preparation for Decision Making Scale (PDMS) [51] as a Post-PtDA outcome measure.

Patient knowledge will be measured using a knowledge test developed by the steering group and embedded within the PtDA. The test will be adapted from the template available on the Ottawa Decision Support Group website [50] and will consist of 4–6 questions about key content important to know when making this decision. This format has been adapted for several clinical conditions and been shown to have high internal consistency and validity. Patient knowledge of their specific pathology and treatment options underlies one of the pillars of informed consent [52], and improved decision quality is based on patients making an informed, value-based decision [13].

The SURE test will be used to screen patients for decisional conflict [31]. It has four questions with ‘yes’ or ‘no’ responses in the domains of certainty, knowledge, values and support. Any ‘no’ answer is indicative of clinically significant decisional conflict. This test has been validated in a range of clinical settings [53, 54].

We will use the Preparation for Decision Making Scale (PDMS) [51] to measure patients’ perceived usefulness of a PtDA in preparing for a medical consultation. This specifically measures the IPDAS criteria for the quality of the decision process. This instrument consists of 10 questions to be ranked on a 5-point Likert scale, has both high reliability and internal consistency with a Cronbach’s alpha of 0.92–0.96 [55].

The survey of orthopaedic surgeons will ask questions about how the PtDA influenced the patient-surgeon encounter. Data collected will aim to quantify experience with the PtDA including (1) number of times and reasons the PtDA was used or not used for eligible patients, (2) if they plan to continue to use the PtDA and (3) barriers and facilitators to implementation in usual clinical care. Specific feedback will be sought with respect on how and when the PtDA can best be administered in the patient journey to optimize uptake by both clinicians and patients. As part of the survey, we will also use the 11-question practitioner version of the PDMS to evaluate clinician views on how effective the PtDA was on the patient encounter [51].

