#### Design of the PtDA

The steps in designing the PtDA prototype include an assessment of decisional needs of patients and clinicians, formulating a format and distribution plan, and reviewing and synthesizing the evidence for inclusion as content [19]. Recent literature demonstrates conflicting clinician opinions on how to advise patients with an Achilles tendon rupture [26, 27], and the first steering group agenda item will be a discussion with clinician and patient members to identify patients’ decisional needs. The steering group will develop and revise the PtDA through an iterative process until consensus is reached on content and structure. The prototype design will be based on the ODSF template [28] and it meets the IPDAS minimal development standards recommended for minimizing risk of bias in PtDAs [16].

The initial prototype will paper-based and drafted in English, with plans for final distribution electronically and printable paper versions available in clinical practice in both English and French translations. Treatment initiation for Achilles tendon rupture is time sensitive thus it is essential that the PtDA be administered to patients soon following injury. With accessibility being a key aspect of PtDA usability, offering both paper and electronic formats will facilitate and maximize patient uptake [29]. The PtDA will be designed knowing that the most common points of first patient contact is the emergency room or outpatient orthopaedic clinic.

The prototype will be written in plain language appropriate for an 8th grade reading level or lower as determined by the Flesh-Kincaid Readability Test Tool [30]. It will be formatted to include: (a) information on Achilles tendon ruptures and specify which patients are eligible for the PtDA, (b) treatment options to consider, (c) summarized evidence on benefits and harms of each approach, (d) a values clarification exercise, (e) space to indicate a preferred treatment option; and (f) the SURE test [31]. The SURE test is a 4-item questionnaire validated for screening for decisional conflict. Probabilities will be presented numerically and in words, with links to graphical representations to facilitate patients’ understanding and adhering to the IPDAS criteria specific to presenting probabilities [32]. There will also be links included for additional information about Achilles tendon ruptures, literature used to develop the PtDA, and treatment specifics including rehabilitation protocols.

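### The scored knowledge test is placed inside the decision aid, against the aid's own content list; followed as written, the pre/post knowledge gain mixes item rehearsal with understanding

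*Protocol article*

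**What the plan says.** All references are to the protocol article.

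- **Where the test sits.** Stage 3, Outcomes and instruments: "Patient knowledge will be measured using a knowledge test developed by the steering group and embedded within the PtDA". It "will consist of 4–6 questions about key content important to know when making this decision".
- **Its role.** In the same section, "patients will complete a knowledge test[50] and the SURE test[31] as a pre-/post-outcome". One test is described, with no parallel form.
- **Content of the aid.** Design of the PtDA lists components (a) to (f), ending with "d) a values clarification exercise, (e) space to indicate a preferred treatment option; and (f) the SURE test". No knowledge test is on the list.
- **Baseline.** Stage 3, Procedure: "The patient will be asked to complete a baseline questionnaire including questions about their demographics", and that questionnaire also carries the secondary outcome measures. The section then describes the patient being splinted and "given a copy of the PtDA to review and complete in preparation for their follow-up appointment in the orthopaedic clinic". The Stage 3 introduction adds that the patient uses the aid unaided at home.
- **Post-test.** After the plaster-room consultation, or up to 2 weeks later, the research assistant gives a questionnaire with the secondary outcome measures.
- **Success rule.** Table 1, knowledge test: "At least 66% demonstrate improvement from pre to post PtDA administration". Data management and analysis makes clear that a nominal improvement is enough.
- **Further use.** The Stage 3 introduction says the pre/post data will serve to size a larger evaluation study.

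**The concern.** An outcome instrument should stand outside the intervention it evaluates. Here the patient would meet the scored items at baseline, again at home while completing the aid with its explanatory text available, and once more at post-test. A correct answer at post-test could then reflect memory of that item as well as understanding gained from the aid, and the design has no control arm to separate the two. Strengths and limitations names patients' own research as a confounder but does not mention repeated exposure to the test items.

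Two things are at stake: the knowledge part of the fifth success criterion, and the knowledge data carried forward to plan the larger study. The primary outcome, feasibility, is not affected.

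**Working it through.** **1. The sections side by side.** Outcomes and instruments puts the knowledge test in the aid. Design of the PtDA does not list it there. Procedure has the secondary outcome measures answered in the emergency department, in a step described before the aid is handed over, so a test that existed only inside the aid could not supply that baseline. The three statements fit together only if the same items appear both on separate questionnaires and in the aid, and even then the content list is incomplete.

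**2. The plan's own figures.** The sample size of 30 rests on precedent, and no effect size or standard deviation is given for knowledge, so there is no formula to reproduce. The accrual arithmetic agrees: 3 per month × 10 months = 30 (12 months would give 36).

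**3. What the criterion requires.** 0.66 × 30 = 19.8, so at least 20 of 30 patients must improve. With 4 to 6 items and no minimum gain, one additional correct answer makes a patient an improver.

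**4. Illustration of sensitivity.** Let k be the number of items (4 to 6, from the protocol), p the proportion correct at baseline, g the chance that rehearsal alone turns an unknown item correct, and t the same chance from all other learning. The values of p, g and t are assumptions; the documents give none. Known items are taken to stay known, and items to be independent.

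- Chance that an unknown item becomes correct: q = 1 − (1 − t)(1 − g)
- Chance that a patient improves: P = 1 − [1 − q(1 − p)]^k
- Chance of meeting the criterion: Pr(X ≥ 20), with X binomial(30, P)

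Rehearsal added to other learning, k = 5, p = 0.5, t = 0.3:

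| g | q | P | Chance of ≥ 20 of 30 |
|---|---|---|---|
| 0 | 0.30 | 1 − 0.85^5 = 0.556 | 0.15 |
| 0.1 | 0.37 | 1 − 0.815^5 = 0.640 | 0.46 |
| 0.2 | 0.44 | 1 − 0.78^5 = 0.711 | 0.77 |

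Rehearsal alone (t = 0), k = 5, p = 0.5:

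| g | P | Chance of ≥ 20 of 30 |
|---|---|---|
| 0.2 | 0.410 | 0.004 |
| 0.3 | 0.556 | 0.15 |
| 0.4 | 0.672 | 0.61 |
| 0.5 | 0.763 | 0.92 |

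The result depends strongly on baseline and item count. At g = 0.4 and p = 0.5 the chance is 0.26 with 4 items and 0.86 with 6. At g = 0.4 and p = 0.7 it is 0.003 with 4 items and 0.10 with 6. In this model rehearsal can only raise the chance; how far is not fixed by anything in the documents.

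**The case against.** The strongest reply has four parts.

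- **The word may be loose.** The content list omits the test and the baseline is taken before the aid is handed over, so the description of the test as part of the aid may only mean that it belongs to the study package. This is possible. It leaves a conflict between sections that needs resolving, and it makes the bias conditional on how that is done.
- **Rehearsal may be intended.** If self-testing is a deliberate part of the aid, the gain is partly a real effect of the package as delivered, and the larger study might test the same package. That has force. But scoring the rehearsed items cannot show whether understanding extends beyond them; different scored items would.
- **Other influences remain anyway.** Clinicians discuss the options in the emergency department and at follow-up, and the baseline form is itself an exposure. This stands: the change below removes one avoidable source of gain, not all of them.
- **The consequences are modest.** Knowledge is secondary, the analysis is mainly descriptive, the article already calls its success endpoints arbitrary, and a missed cutoff leads to discussion by the steering group. This stands too.

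A reader might also infer that patients answer the post-test with the answers in hand, so that the post score is demonstrably inflated. The documents do not support that. No section mentions an answer key, and the post measure is a separate questionnaire from the research assistant, with no statement that the aid is available then. Access to the text applies only to a copy completed at home.

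**Conclusion.** The point holds in a limited form. The protocol contradicts itself on whether the knowledge test is in the aid. If the section on outcomes is followed, the outcome instrument becomes part of the intervention, and the knowledge gain is likely biased upward because it combines item rehearsal with understanding.

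The size cannot be computed. The figures above show only that a one-item rule on a 4 to 6 item test is sensitive to modest rehearsal under some assumptions. Under others (a high baseline, or a small rehearsal effect) rehearsal alone would rarely meet the 66% criterion, so it would be wrong to conclude that the criterion is bound to be met. What is affected is a secondary criterion and the knowledge data for sizing the larger study; the primary feasibility outcome is untouched.

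The SURE test raises a related but lesser point: the content list explicitly places it in the aid, and it too is a pre/post outcome.

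**What to change.** 1. Make Outcomes and instruments and Design of the PtDA agree on whether the knowledge test is in the aid.
2. Give the scored knowledge items only on a stand-alone form: in the emergency department before the aid is handed over, and again at the post-test without the aid at hand.
3. If the aid keeps self-check questions, use items different from the scored ones.
4. State that a residual retest effect from the baseline form, and the effect of the clinicians' discussions, remain in the pre/post difference.
5. Take the post SURE score from the research assistant's questionnaire, and note the repeat exposure, since SURE is also listed inside the aid.

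The cost is a wording change and a separately printed form. The downside is a few extra items to write, or loss of the embedded self-check.
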